### Randomization and blinding

The process of randomization will be carried out by the software REDCap (automatically, without contact with the researcher) after the baseline evaluation. Subjects will be allocated to one of the intervention groups (1:1:1), which will have the same number of participants each: walking aid (WA) group; walking aid with telemonitoring (WAT) group; control group. The WA group will be trained for the use of a walking aid and receive guidance on safe gait but will not receive telemonitoring. The WAT group will receive training for the use of a walking aid, guidance on safe gait, and telemonitoring. The control group will receive only guidance on safe gait.

This study will be blind for the researchers involved in the post intervention assessments and the researcher who will analyze the data. Also, the data will be analyzed by a researcher who is not involved in the interventions nor the assessments.

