#### Assessment moments

Baseline assessment will be carried out before randomization and interventions. Assessment of gait speed and fear of falling will be repeated immediately after the intervention. Fear of falling, life-space mobility, functionality, quality of life, fall history, cognition and mood assessments will be repeated 3 and 6 months after intervention by a telephone interview or video call.

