#### Gait assessment

Timed Up and Go test (TUG) evaluate mobility, balance, gait, and risk of falling [15]. In TUG, the researcher requests the participant to stand up on the chair (without using arms), walk 3 meters, go around outside a cone, walk back to the chair, and sit down without using arms [16]. Patients will be instructed to perform the test at the highest possible speed three times and the average of them will be used as the result [16].

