### Outcomes

#### Primary outcome

The primary outcome will be fear of falling.

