### Statistical analysis

Continuous variables will be expressed on average and standard deviation or median and interquartile interval 25%-75%. Categorical data will be presented in absolute and relative numbers. To verify the distribution normality of data, the Shapiro-Wilk normality test will be applied. For comparisons between groups over time, One-way ANOVA test for parametric data or Kruskall-Wallis for non-parametric data will be used. For intragroup analyses, repeated measures Analysis of Variance (RM-ANOVA) test for parametric data or Friedman test for non-parametric data will be used. Only for the Time Up and Go variable before and after intervention, a paired t-test will be used for parametric data, or a Wilcoxon test will be used for non-parametric data. For intergroup and intragroup analyses, the baseline, 3 and 6 months after discharge from the geriatric ED will be considered. To evaluate correlations, the Pearson correlation test will be used for parametric data and the Spearman test will be used for non-parametric data. All the analyses will be carried out using the Statistical Package for Social Sciences (SPSS) version 28.0.1 (SPSS Inc.^®^; Chicago, IL, USA), considering a significance level of 5%.

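### As written, post-intervention TUG has only a within-arm paired test and the immediate FES-I has no listed analysis, so neither is compared between the randomised arms

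*Protocol article*

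**What the plan says.** Under Assessment moments, two measures are taken again in the ED: "Assessment of gait speed and fear of falling will be repeated immediately after the intervention". The later visits, by telephone or video call, carry a different list: "Fear of falling, life-space mobility, functionality, quality of life, fall history, cognition and mood assessments will be repeated 3 and 6 months after intervention". No gait test is in it. Gait assessment describes one test, the TUG: "Patients will be instructed to perform the test at the highest possible speed three times and the average of them will be used".

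Statistical analysis gives a general between-group rule: "For comparisons between groups over time, One-way ANOVA test for parametric data or Kruskall-Wallis for non-parametric data will be used". It names repeated-measures ANOVA or Friedman for intragroup analyses and then makes an exception: "Only for the Time Up and Go variable before and after intervention, a paired t-test will be used for parametric data", with Wilcoxon as the non-parametric alternative. The time points come next: "For intergroup and intragroup analyses, the baseline, 3 and 6 months after discharge from the geriatric ED will be considered".

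The design has a concurrent randomised control: "The control group will receive only guidance on safe gait". On the primary endpoint the protocol says: "The primary outcome will be fear of falling". Mobility is among the secondary outcomes.

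**The concern.** The trial sets out to measure efficacy and randomises a control arm to do so. For TUG, the only test named looks at change within an arm. Every participant performs maximal-speed trials, receives at least safe-gait guidance, and soon afterwards performs the trials again during an acute illness episode. Familiarity with the test, fatigue and short-term recovery can move TUG in all three arms. A paired test asks whether an arm's mean change differs from zero, not whether it differs from the control arm's change.

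What is at stake is the immediate effect of training on gait. These are the only post-intervention gait data the trial will have, and the analysis named for them does not use the randomisation. The immediate FES-I has a related gap: it is collected in all arms, but no sentence assigns it a test.

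**Working it through.** **Step 1. Which measurements fall within which analysis** (from Assessment moments, Gait assessment and Statistical analysis; gait speed is read as TUG, the only gait test described).

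| Measure | Baseline | Immediately after | 3 months | 6 months |
|---|---|---|---|---|
| TUG | yes | yes | no | no |
| FES-I | yes | yes | yes | yes |
| Time points listed for intergroup analyses | yes | no | yes | yes |

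The only TUG value inside the listed intergroup time points is the baseline one. Post-intervention TUG appears only in the paired test, and the immediate FES-I appears in no test.

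**Step 2. How a paired test behaves when all arms change alike.** The plan states no power figure for TUG, so there is none to reproduce. Inputs:
- n = 51 per arm (Sample). This number was derived for FES-I.
- Significance level 5% (Statistical analysis). Two-sided is assumed.
- Common retest gain d, in units of the SD of the change score. The documents give neither a TUG SD nor a retest effect, so d = 0 to 0.5 is an assumption shown as a range.
- Treatment effect: zero.

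The paired t statistic follows a noncentral t distribution with n − 1 = 50 degrees of freedom and noncentrality d√n = d × 7.141. The critical value is 2.009. The probability of a significant change is P(|T| > 2.009).

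| d | Noncentrality | One arm | At least one of the two walking-aid arms |
|---|---|---|---|
| 0 | 0 | 0.05 | 0.10 |
| 0.1 | 0.71 | 0.11 | 0.20 |
| 0.2 | 1.43 | 0.29 | 0.49 |
| 0.3 | 2.14 | 0.56 | 0.80 |
| 0.4 | 2.86 | 0.80 | 0.96 |
| 0.5 | 3.57 | 0.94 | 0.996 |

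The last column is 1 − (1 − p)², where p is the one-arm probability. With 42 per arm, the one-arm probabilities for d = 0.1 to 0.5 are 0.10, 0.24, 0.48, 0.72 and 0.89.

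**Step 3. The unit matters.** If the same gains are expressed in SDs of a single measurement's within-person error, the SD of change is √2 times larger and d shrinks by that factor. At n = 51, gains of 0.3, 0.4 and 0.5 in that unit give 0.32, 0.51 and 0.70.

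**Step 4. A between-arm test under the same conditions.** In 20,000 simulated trials with 51 per arm and the same shift in every arm (d = 0, 0.2, 0.3, 0.4), one-way ANOVA on the TUG change rejected in 4.9% to 5.3%. A shift common to all arms cancels.

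**Step 5. Reading three paired tests side by side.** In the same simulations, at least one walking-aid arm was significant while control was not in 9%, 36%, 36% and 19% of trials for d = 0, 0.2, 0.3 and 0.4. Setting the control arm's p-value beside the others does not replace a direct comparison.

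**The case against.** The strongest reply is that the TUG exception follows the intragroup sentence. It may therefore replace only repeated-measures ANOVA, which is not needed with two time points, and leave the general one-way ANOVA rule open to TUG. The time-point sentence cannot be exhaustive for TUG either, because the paired TUG test is itself intragroup and uses a visit that the sentence omits. This reading is possible. But no sentence provides a between-arm test at the immediate visit, and the one sentence that lists intergroup time points leaves that visit out. If a comparison is intended, the text still needs to say so.

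A reader might infer that the protocol will present a within-arm gain as efficacy, or that the control arm's TUG data are wasted. The documents support neither. No sentence says how a within-arm change will be interpreted, and the paired test is not limited to the trained arms, so a parallel gain in controls would be seen. Nor does the protocol say that the immediate FES-I will be discarded; it is only absent from the listed analyses.

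The size of any retest effect is also unknown. Fatigue would work against practice, and at a gain of 0.1 the excess over 5% is small. Finally, the 3- and 6-month FES-I and life-space comparisons are untouched by the TUG test, and TUG is not named individually as an outcome; it enters through mobility. These points limit the weight of the concern but do not supply the missing comparison.

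**Conclusion.** The point holds as a defect in the stated analysis, beyond detail that could be left to an analysis plan: the article names the TUG test and the intergroup time points, and together they give no randomised comparison of post-intervention TUG or immediate FES-I. That conclusion rests on the text alone.

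Its numerical size rests on assumptions: a gain common to all arms, no treatment effect, 51 analysed per arm, two-sided 5%, and gains in units of the SD of change. Over 0.1 to 0.5 SD, the chance of a significant change in a given arm runs from 0.11 to 0.94, while a between-arm test stays near 5%. The matter should be corrected. It does not affect the primary outcome at 3 and 6 months.

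**What to change.** In Statistical analysis:
1. Compare post-intervention TUG between the randomised arms by ANCOVA adjusted for pre-intervention TUG, and report adjusted differences with 95% confidence intervals.
2. Analyse the immediate FES-I in the same way, adjusted for baseline FES-I and labelled as a secondary time point.
3. Add the immediate post-intervention visit to the time points listed for intergroup analyses.
4. Keep paired within-arm changes as descriptive.

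A three-arm ANCOVA is enough. Pooling the two walking-aid arms against control at this visit is an option, because telemonitoring starts only after ED discharge (Telemonitoring). It would reduce the variance of the contrast by 25% relative to 51 versus 51: (1/102 + 1/51) ÷ (2/51) = 0.75. If used, the pooling should be stated in advance.

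The cost is a few sentences in the statistical section, with no new data or visits.

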Finally, new technologies have been developed to improve health care, including telemonitoring. Telemonitoring is defined as the use of information technology and telecommunications for remote health care [9] and its main advantages are reducing unnecessary visits and home visits, reducing the risk of infections, monitoring the rehabilitation process, and improving patient compliance [10]. However, most studies related to telemonitoring are carried out with patients who have chronic diseases. Also, there are no data on the effects of an intervention encompassing gait devices, associated or not with telemonitoring, to improve the mobility of older patients admitted to the ED despite recommendations from international societies and the Geriatric Emergency Department Accreditation (GEDA) accreditation [3].

The hypothesis of the study is that the provision of walking aids enhances mobility in living spaces and will have a significant impact on fear of falling, functionality, and quality of life. Therefore, this study aims to evaluate the efficacy of a program of training and provision of walking aids, associated or not with telemonitoring, on fear falling, mobility, quality of life, and risk of falls up to 3 and 6 months in older adults cared for in an ED. In addition, we hypothesize that fear of falling may be correlated with lower scores in mobility, quality of life, and risk of falls.

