### Sample

Sample size calculation was based on Morgan and cols study, which described a minimal detectable change (MDC_95_) of 8,2 points on Falls Efficacy Scale International (FES-I), with a standard deviation of 12 points [11]. For the calculation, ANOVA sample size was used, and three groups were considered. For an α of 0.05 and a power of 0.80, the total sample size was computed as 42 individuals. Due to the estimated loss of 20% during follow-up, the sample necessary for the success of the study was expanded to 153 individuals, 51 in each group (randomization 1:1:1).

We will include patients aged 65 years or older, admitted to the Geriatric ED of Hospital Sírio-Libanês, willing and able to give informed consent and with at least one of the following for indication and training of mobility aids: reduction of postural instability; improvement of motor control; increase of somatosensory feedback; reduction of biomechanical overload; safe promotion of autonomy; fall history (in the last six months). Exclusion criteria will include altered level of conscience, need for supplemental oxygen (≥3L/min), respiratory distress, hemodynamic instability, postural instability with a tendency to fall backward, cognitive impairment that limits the use of walking aids, hospitalization after ED evaluation, and delirium.

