#### Quality of life

Quality of life will be evaluated by Euro Quality of Life Instrument-5D (EQ-5D) [28]. This instrument covers five health dimensions: mobility, self-care, usual activities, pain/discomfort, and anxiety/depression [29]. Each dimension is classified into 3 levels: no problems (1 point), some problems (2 points), and extreme problems (3 points) [30]. The results will be presented as frequency distributions of levels and dimensions over time, including changes within dimensions [29].

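### The correlation analysis for fear of falling names neither visit nor handling of arm; if follow-up data are pooled over arms, it should be adjusted for arm

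*Protocol article*

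**What the plan says.** Besides the treatment hypothesis, the Introduction of the protocol article states: "we hypothesize that fear of falling may be correlated with lower scores in mobility, quality of life, and risk of falls".

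Statistical analysis gives one sentence on method: "To evaluate correlations, the Pearson correlation test will be used for parametric data and the Spearman test will be used for non-parametric data". It names no visit, does not say whether the arms are pooled, and mentions no adjustment or stratification. The sentence on time points concerns other analyses: "For intergroup and intragroup analyses, the baseline, 3 and 6 months after discharge from the geriatric ED will be considered".

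Three further places matter:

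- Assessment moments: "Baseline assessment will be carried out before randomization and interventions". FES-I, life-space mobility, quality of life and fall history are then repeated at 3 and 6 months.
- Fall history and Secondary outcomes: falls as an outcome are collected during follow-up, so they exist only after allocation.
- Quality of life: each EQ-5D dimension is coded "no problems (1 point), some problems (2 points), and extreme problems (3 points", so a higher level is worse.

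**The concern.** The trial's main hypothesis is that walking aids change fear of falling, life-space mobility and quality of life. These are the variables to be correlated. Two of the three arms receive an aid. If the aid works, those arms differ from control on both variables at follow-up, and a correlation over all participants picks up that difference. It would appear as an association even if, within any one arm, more fearful patients were no less mobile than the others. A stated hypothesis could then be called supported because of the treatment effect.

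A smaller point concerns direction. The hypothesis speaks of lower scores throughout. That fits the Life-Space Assessment (LSA), where higher means greater life space. It does not fit EQ-5D levels as coded, or falls, where the expected association with fear is with higher values.

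**Working it through.** The documents give no figure for the correlation analysis, so there is none to reproduce. The check asks how far pooling moves r and its test.

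**Inputs from the protocol (Sample)**
- FES-I: "minimal detectable change (MDC_95_) of 8,2 points on Falls Efficacy Scale International (FES-I), with a standard deviation of 12 points", so d1 = 8.2/12 = 0.683 in size. It is taken as negative (less fear with an aid), with 12 as the within-arm SD.
- Three arms, 1:1:1, 51 each, 153 in total, 20% loss: 153 × 0.8 = 122.4, about 122 with data (41 per arm).
- 5% significance level (Statistical analysis), taken as two-sided.

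**Assumptions**
- Both aid arms shift equally, so two thirds of participants are treated.
- The second measure shifts by d2 SD. The documents give no value, so 0 to 0.68 is shown, in the beneficial direction on a scale where higher is better.

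**Formula.** With fractions 1/3 and 2/3, the between-arm covariance is (1/3)(2/3)·d1·d2 = (2/9)·d1·d2, and the variances follow in the same way. For within-arm correlation ρ:

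pooled r = (ρ + (2/9)·d1·d2) / √[(1 + (2/9)·d1²)(1 + (2/9)·d2²)]

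**No within-arm correlation (ρ = 0)**
- (2/9) × 0.683² = 0.104.
- d2 = 0.4: numerator −(2/9)(0.683)(0.4) = −0.061; denominator √(1.104 × 1.036) = 1.069; r = −0.057. By Fisher's z with n = 122, 0.057 × √119 = 0.62, and a 5% test rejects in 9.5%.
- d2 = 0.6: r = −0.083, rejection 14.9%.
- d2 = 0.683: r = −0.104/1.104 = −0.094.

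Simulation of the plain Pearson test (8,000 runs per setting, ρ = 0):

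| Arm means on FES-I | d2 | r | Rejects, 51 per arm | Rejects, 41 per arm |
|---|---|---|---|---|
| 0, d, d | 0 | 0.00 | 5% | 5% |
| 0, d, d | 0.2 | −0.03 | 6% | 6% |
| 0, d, d | 0.5 | −0.07 | 14% | 12% |
| 0, d, d | 0.68 | −0.09 | 22% | 18% |
| 0, d/2, d | 0.5 | −0.05 | 10% | 9% |
| 0, d/2, d | 0.68 | −0.07 | 15% | 12% |

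Adjusted for arm, the partial correlation averaged zero and rejected in 4.5% to 5.3% in every setting. The runs used Pearson on normal data; Spearman was not run separately, but arm differences enter pooled ranks by the same route.

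**Effect on FES-I alone (d2 = 0).** There is no inflation, only attenuation: ρ = −0.40 becomes −0.40/√1.104 = −0.38.

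**Real within-arm correlation, hypothesised direction.** With ρ = −0.30 and d2 = +0.4, r = (−0.30 − 0.061)/1.069 = −0.34.

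**Baseline.** No treatment has been given, so d1 = d2 = 0 and r = ρ.

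**The case against.** The strongest reply is that the article does not commit to the analysis criticised. It fixes neither visit nor pooling, a baseline or within-arm correlation would fit its sentence equally well, and a condensed article may leave such detail to a fuller document. This stands, and it is why the point is conditional. What keeps the point alive is that falls as an outcome arise only after allocation. A follow-up correlation is therefore a natural reading, and for it the named method is the weaker choice.

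A reader might infer that the treatment effect will distort this analysis as planned. The documents do not support that. Distortion needs follow-up data, pooled arms and a real effect, and a false-positive excess needs an effect on both variables.

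A reader might also infer that pooling will hide a true association, because the LSA composite takes account of independence and an aid could lower it. If the aid arms scored 0.4 or 0.6 SD lower, ρ = −0.30 would shrink to −0.22 or −0.19, and power at n = 122 would fall from 92% to 70% or 56%. The direction is conceivable, but no figure supports a shift of that size, and it runs against the trial's own hypothesis that aids enhance mobility. Likewise, a pooled r of −0.24 with 86% rejection needs arm means of 0, d and 2d on both outcomes, an extreme case with no basis in the protocol.

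Finally, the mismatch in sign might be read as meaning that expected results would count against the hypothesis. No one-sided test is stated and no EQ-5D summary score is defined, so this is loose wording and would not by itself produce a wrong conclusion.

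**Conclusion.** The point holds in conditional form and is minor. If 3- or 6-month values are pooled over arms and the aid affects both measures, r moves by about 0.06 to 0.09 at the design effect, and the false-positive rate of a nominal 5% test rises to roughly 10% to 20%. In the hypothesised direction, the shift in the mobility correlation favours the hypothesis. These figures rest on the full 8.2-point effect in both aid arms, an SD of 12, and an assumed 0.4 to 0.68 SD effect on the second measure. They are smaller if telemonitoring accounts for half of the effect, and the inflation vanishes if only FES-I responds. This is a secondary hypothesis; the primary outcome, the between-arm comparisons and the sample size are not affected.

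**What to change.** Add two or three sentences to Statistical analysis:

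1. For mobility and quality of life, test the hypothesis on the baseline values of all randomised participants, which precede allocation.
2. At 3 and 6 months, including for falls during follow-up, use a partial Pearson or Spearman correlation adjusted for arm, separately at each visit. Falls belong here because a fall in the last six months is one of the alternative inclusion criteria, so selection shapes the baseline link between falls and fear.
3. Reword the hypothesis with the expected sign for each measure as scored: negative for the LSA, positive for EQ-5D levels (by dimension, as no summary score is defined) and for number of falls.

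The cost is this text and a routine analysis option. No new data, visits or participants are needed.

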## Discussion

International guidelines for Geriatric ED exist to guide and promote best practices for older patients [3, 4]. The American College of Emergency Physicians created an accreditation for geriatric EDs that abide by their recommendations and Hospital Sírio-Libanês was awarded a Level 3 (Bronze) for the first time in 2019, being the first hospital in the South Hemisphere with this recognition [3]. Although the provision of walking aids in the Geriatric ED is recommended in American and European guidelines [3, 4], it is based mainly on expert opinion and there is a lack of trial data on the impacts of training and provision of walking aids in this acute setting. Therefore, this study aims to be the first randomized controlled trial to evaluate this intervention, associated or not with telemonitoring.

Older adults have changes inherent to age, such as sarcopenia, decreased strength and muscle mass, and balance and gait disorders, which predispose to a greater risk of falls [41, 42]. Different than other studies carried out in Geriatric ED, the primary outcome will be the older patient’s fear of falling and the secondary outcomes will focus more on mobility than on falls and its consequences. With this strategy, this study aims to evaluate the impact of the walking aid on fear of falling, mobility and autonomy of older adults admitted to a Geriatric ED.

Previous studies carried out with older adults in the ED that explored fear of falling were mainly observational and aimed at its impact on risk and number of falls, ADL and quality of life [43–45]. On the other hand, experimental studies in older patients that assessed fear of falling were carried out exclusively in other environments, such as ambulatory settings [46]. Finally, Goldberg et al. carried out a randomized controlled trial aimed to determine if a fall prevention program in the ED could reduce revisits and hospitalizations related or not to falls, but, despite including in this program a physical therapist assessment, there was no training and provision of walking aids [47].

Telemonitoring has been more frequently studied in older adults, but mainly in ambulatory settings and focused on chronic illnesses [48–50]. In this study, the intervention will be evaluated in acutely ill older patients admitted to a Geriatric ED and trained in the use of walking aids. In addition, in a randomized clinical trial, telemonitoring could be an additional strategy to reduce the loss of follow-up of participants during the study.

Finally, to the best of our knowledge, there are no previous studies that have compared groups according to the provision of gait assistance devices and used FES-I as a main outcomes. Therefore, we’ve calculated the sample size using as a reference the study by Morgan et al. [11] which proposed a gait assistance device intervention in its participants and had a higher reported DMC than other initiative [51] but conducted intragroup comparisons. In addition, our study will also address intragroup differences when comparing baseline, 3 and 6 months after discharge from the geriatric ED.

A limitation of the study protocol is that it will be performed in a single center. However, having been described in detail, registered in a public database, and published in an open-source journal, it might be replicated by other research groups around the globe. In addition, another limitation of the study is that participants in the control group may initiate the use of assistive gait devices over the 6-month study period. However, this identification will be possible through the LSA questionnaire. After completion of the study and blind analysis of the data by the statistician, the percentage of individuals in the control group who initiated the use of gait devices will be shown. If there are patients in the control group who initiated the use of a gait device, it will be considered a protocol deviation from the assessment point at which they started using the assistive gait device, which may be 3 or 6 months after discharge from the geriatric ED service. Consequently, a secondary analysis will be presented without the protocol deviation values.

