#### Mobility in life-space

Mobility in life space will be a secondary outcome of the study and will be assessed by the LSA, which allows the characterization of mobility in life-spaces (other rooms of your home besides the room where you sleep; to an area outside your home, places outside your neighborhood but within your town; and to places outside your town), specifically frequency, need for mobility aids and the help of third party in the last 4 weeks [14]. Four indicators are calculated (with the highest scores indicating greater life space):

Independent life-space: the highest life-space level attained without help from a person or mobility aid.Life-space using equipment: the highest life-space level attained when a mobility aid was used, without help from a person.Maximal life-space: the highest life-space level attained with the help of a person or mobility aid.Composite score: encompasses distance, frequency, and level of independence, with a range from 0 to 120.

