#### Fall history

Fall is a sudden and involuntary transfer of the body to the ground or a lower level [33]. Fall history will be evaluated periodically during the study and the patients must fill out a diary to register every moment in which they fall, and at the end of the study, this data (including location, associated injuries, need for special care after the fall) and the total number of falls will be evaluated.

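### Walking-aid use in controls is to be identified through the LSA, whose 4-week recall at months 3 and 6 misses use that starts and stops between the windows

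*Protocol article*

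**What the plan says.** The limitations paragraph of the Discussion recognises that "participants in the control group may initiate the use of assistive gait devices over the 6-month study period". It names one means of finding them: "However, this identification will be possible through the LSA questionnaire". Three commitments follow:

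- A descriptive figure: "the percentage of individuals in the control group who initiated the use of gait devices will be shown".
- A rule that such use is a "protocol deviation from the assessment point at which they started using the assistive gait device, which may be 3 or 6 months after discharge".
- An analysis: "Consequently, a secondary analysis will be presented without the protocol deviation values".

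The section Mobility in life-space describes what the LSA records: "specifically frequency, need for mobility aids and the help of third party in the last 4 weeks". The section Assessment moments lists life-space mobility among the measures repeated after the ED visit; that sentence ends "quality of life, fall history, cognition and mood assessments will be repeated 3 and 6 months after intervention by a telephone interview or video call". The LSA is therefore given at baseline, 3 months and 6 months.

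Two other follow-up contacts are described. Under Fall history, "the patients must fill out a diary to register every moment in which they fall"; the listed contents of the diary concern falls and their consequences, not aid use. Under Telemonitoring, the fortnightly calls are for the WAT group only, so controls have none.

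**The concern.** The article promises detection over six months from an instrument that looks back four weeks on two occasions. A control participant who obtains a cane soon after discharge, uses it for a month and puts it away would report no aid at either call. That person would be counted as never having started.

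Two stated outputs rest on this flag. The percentage of controls who took up an aid could be too low. The secondary analysis, meant to exclude values affected by control-group aid use, could retain some of them. The second effect also reaches the secondary outcome of falls within three months: falls accumulate over the whole interval, while aid use is observed only in its last four weeks. An analysis plan cannot repair this later, because the information would never have been collected.

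**Working it through.** The article gives no figure for LSA coverage or for control-group uptake, so there is nothing to reproduce. The check compares the recall windows with follow-up time.

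**Inputs**
- Recall window: 4 weeks (Mobility in life-space).
- Calls: 3 and 6 months (Assessment moments), taken as weeks 13.04 and 26.09.
- Period in which use may start: 6 months (Discussion).
- Assumption, not in the article: one episode of use lasting L weeks, with its start uniform over follow-up.

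**Coverage**
- Window 1: 13.04 − 4 = 9.04, so weeks 9.04 to 13.04.
- Window 2: 26.09 − 4 = 22.09, so weeks 22.09 to 26.09.
- Weeks covered: 8 / 26.09 = 31%. Unobserved: about 9 weeks at the start of each interval, 18 in all.

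**Share of episodes missed**

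An episode is missed only if it lies wholly inside one unobserved stretch. For L below 9.04 the start must fall in the first 9.04 − L weeks of an interval of 13.04 weeks:

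share missed = (9.04 − L) / 13.04

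| Length of use | Calculation | Missed |
|---|---|---|
| 1 week | 8.04 / 13.04 | 62% |
| 2 weeks | 7.04 / 13.04 | 54% |
| 4 weeks | 5.04 / 13.04 | 39% |
| 6 weeks | 3.04 / 13.04 | 23% |
| 8 weeks | 1.04 / 13.04 | 8% |
| about 9 weeks or more | – | 0% |

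**Sensitivity to the uniform start.** If use starts on the day of discharge, every episode shorter than about 9 weeks is missed. If it starts within the four weeks before a call, none is. The table lies between these extremes.

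**Placement at 3 or 6 months.** A single episode that starts before month 3 and escapes window 1 must have ended by week 9.04, so it cannot reach window 2. A single episode is therefore either missed or assigned to its own interval. Misplacement needs stop-and-restart use. For example, use in weeks 2 to 6, none in weeks 9 to 13 and use again near month 6 would be logged as starting at 6 months, and the 3-month value would be kept.

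**The case against.** The strongest reply is that the LSA does most of what the article needs. The deviation rule works by assessment point and needs no calendar date. Comparing the baseline, 3-month and 6-month LSA gives that point for anyone still using the aid at a call. A reader might infer that the start of use cannot be placed at all; the documents do not support this, since placement fails only for stop-and-restart use. This part of the reply stands.

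A reader might also take the 31% of weeks covered as the share of users detected. It is not: any use of about 9 weeks or more is always found.

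Nor do the documents show that brief use is the usual pattern, that much of the control arm would use an aid, or that the early weeks matter most. The eligibility criteria (postural instability, motor control, fall history and so on) are compatible with sustained use. The primary outcome, FES-I, is measured after the ED visit at the same two calls, so aid use current at that moment is captured. The flag feeds a descriptive percentage and a secondary analysis, not the between-group comparison under Statistical analysis. The reliance on the LSA is stated for control-group uptake only, so the point does not extend to a claim about adherence in the WA and WAT groups. All of this stands and limits the size of the point.

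It can also be said that an article leaves interview items to the full protocol. That does not answer the point: the article names the LSA as the method and describes its recall window, and the two do not fit the claim made for them.

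**Conclusion.** The point holds in a limited form. As described, the LSA cannot identify all control participants who start using an aid over the six months; it identifies those using one in the four weeks before each call. Apart from misreporting, the error runs one way, towards too low a percentage, and the secondary analysis may keep some controls who used an aid.

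The size depends on how long use lasts: from 54% of episodes missed at 2 weeks to 8% at 8 weeks and none from about 9 weeks, assuming a single episode and a uniform start. The documents give no uptake rate and no duration of use, so the undercount in percentage points cannot be stated.

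A reader might go further and infer that a null result for walking aid against control would be uninterpretable. The documents do not support that: the main comparison is computed without the flag, and nothing shows that brief, unseen use would be common. The change is worth making because it is cheap and corrects a stated method that cannot deliver what is claimed for it.

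**What to change.** At the 3- and 6-month interviews, ask control participants, and preferably all three arms, whether they have used a cane or walker at any time since ED discharge (at month 3) or since the last interview (at month 6), with approximate start and stop. Put the question after the FES-I so that it cannot colour the primary outcome. Use the answer together with the LSA for the control-group percentage and for the deviation flag. Correct the Discussion so that a figure from the LSA alone is described as use in the last 4 weeks.

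The cost is about a minute in each of two calls already planned and an added REDCap field. The drawback is recall over about three months in older adults, so the dates should be treated as approximate. The LSA item remains the better record of recent use, which is why the two should be used together.
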